# STUDY DESIGN

**3.1** **Methodology**

This is a multicentre intra-patient randomised controlled longitudinal observational cohort study, with parallel assignment, single blinded clinical trial to test the effect of ablative fractionated CO_2_ laser on hypertrophic scarring. Two anatomically comparable and independent scars would be selected per subject and randomly allocated to receive either fractioned CO_2_ laser therapy or standard care. An independent assessor will be blinded to the intervention and the control scars sites.

The study will collect quantitative data through tissue and blood samples to assess the cellular and molecular biomarkers response to laser therapy and qualitative data using a series of patient reported outcome measures (PROMs) and scar assessments. Scars will be subjectively assessed using the standard of care scar assessments; Modified Vancouver Scar Scale (mVSS), Patient and Observer Scar Assessment Scale (POSAS)*,* Brisbane Burn Scar Impact Profile (BBSIP). Scars will also be objectively assessed using 3D Vectra Photography for scar site identification, high resolution ultrasound for thickness, Cutometer^®^ for elasticity and colour using DSMII Colorimeter® camera.

As part of the evaluation of the impact of laser treatment on patients’ quality of life a PROMS validation study will be carried out to evaluate if the BBSIP is a useful tool for evaluating the impact of laser therapy on scar tissue and quality of life.

PROMs describe how the patient is functioning or feeling without input from clinical staff (17) providing a unique perspective of patients’ lived experience of the disease as not all symptoms or impacts are obvious to clinicians (18). In order for PROMs to be effective in clinical trials and practice, they have to capture information on domains that matter to the patient (17).

A previous study carried out in Birmingham (13) identified that there were a number of important domains for patients with burn injuries and these were applicable when evaluating relevant interventions. These include: scarring, movement and function, scar sensation, psychological distress, body image and confidence, engagement in activities, treatment burden and impact on relationships.

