## Randomisation

**5.4.1 Randomisation Procedures**

Each patient will have their own control scar in an anatomically comparable site either on the trunk or limbs. Allocation of scar treatment will be performed using randomisation. Two comparable anatomically scarred areas > 25 cm^2^ on trunk, arms or legs will be identified on the same patient and will be described as location A and location B on the body map. The patient’s identified scar site, A and B, will be randomised on a 1:1 basis to either the standard of care or laser treatment as shown in Table 1.

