## Statistical Analysis

The primary comparison groups will be the scar sections randomised to (control group) versus those randomised to treatment with laser therapy (experimental group). Outcome data will be collected at pre-laser, 3 weeks post the first and third treatments and 12 month

s post third treatment.

All analysis will be based on the intention to treat principle, i.e. all scars will be analysed in the treatment group to which they were randomised irrespective of compliance with the allocated treatment or other protocol deviation. The data analysis for this pilot trial will be descriptive and mainly focus on confidence interval estimation, with no formal hypothesis testing performed.

Dichotomous feasibility measures, like the recruitment and retention rates, including completeness of data will be reported as numbers and percentages. These values will be summarised across participants or treatment groups as appropriate.

Given this study is a pilot, the data will help inform the selection of the most appropriate primary outcome measure for a larger RCT and provide data to estimate the sample size required for the main RCT.

Analysis methods will be chosen according to the data type; 1. Continuous endpoints (e.g. VSS total score): These data will be summarised using means and standard deviations, with differences in means with 95% confidence intervals reported. Longitudinal plots of the data over time will also be constructed for visual presentation of the data. 2. Categorical (dichotomous) endpoints (e.g. rates of improvement in scar domains): The number and percentages of participants/scars experiencing the event will be summarised across and between groups.

As this is a randomised study, there are no priori subgroup analyses specified.

Every attempt will be made to collect full follow-up data on all study participants with the anticipation that missing data will be minimal. The assessment of missing data is an outcome measure of this study.

If a suitable primary outcome is identified during the pilot trial, the level of missing data will form one component of the assessment of feasibility for a future trial. As this is a pilot trial, no formal sensitivity analysis will be conducted.

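### Section 8.2 describes the laser versus control comparison in two-group terms although every patient supplies both scars; it should name a within-patient contrast and report its SD

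*Protocol*

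**What the plan says.** The design is within-patient. Protocol section 3.1 states: "Two anatomically comparable and independent scars would be selected per subject and randomly allocated". Section 5.4.1 adds: "Each patient will have their own control scar in an anatomically comparable site either on the trunk or limbs". Table 1 gives the two possible allocations, each placing laser on one location and standard care on the other. The treatment schedule (section 6.1) has both areas assessed before randomisation and before each laser session. Sections 7.5.1 and 7.5.6 and Appendix A have both scars biopsied at baseline and at the final visit.

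Section 3.1 nevertheless labels the trial a "multicentre intra-patient randomised controlled longitudinal observational cohort study, with parallel assignment".

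Section 8.2 defines the comparison this way: "The primary comparison groups will be the scar sections randomised to (control group) versus those randomised to treatment with laser therapy (experimental group)". For continuous endpoints it continues: "These data will be summarised using means and standard deviations, with differences in means with 95% confidence intervals reported". For dichotomous endpoints: "The number and percentages of participants/scars experiencing the event will be summarised across and between groups". It describes the analysis as descriptive, built on interval estimation without tests, and says the data will help to size a later, larger trial. The one model in section 8.2 that could carry a patient effect, a linear mixed-effects model, is assigned to the search for drivers of a good response, not to the laser versus control contrast.

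**The concern.** The two groups in section 8.2 are the same people. Two comparable scars on one person share age, skin type, mechanism of injury and healing tendency, so their outcomes are likely to be positively correlated. That is the statistical reason for using a patient as their own control. A summary by group means and group SDs does not use that correlation, and the parallel label in section 3.1 points an analyst towards an interval for independent samples.

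Two of the pilot's stated products are at stake. One is the precision of the interval estimates, which are its main analytical output. The other is its value for planning: a further within-patient trial needs the SD of the paired difference, or equivalently the group SDs together with the within-patient correlation, and section 8.2 lists neither the paired SD nor the correlation among the quantities to be reported.

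**Working it through.** **Inputs from the Protocol.** 60 participants and a 20% allowance for drop-out (section 8.1.1); one laser and one control scar per patient (sections 3.1 and 5.4.1); 95% intervals (section 8.2).

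**Input not in the Protocol.** The within-patient correlation r of the outcome between the two scars. It is assumed here, over the range 0 to 0.7. Results are in units of the SD of a single scar's outcome, taken as equal in the two groups.

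**The plan's own figure.** The Protocol gives no effect size, SD or power. It does give a maximum interval width of 25% for retention. With 60 participants, 2 × 1.96 × √(0.25/60) = 0.253, so that figure reproduces. It does not depend on pairing.

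**Completers.** 60 × 0.80 = 48 pairs.

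**Half-width if the scars are treated as two independent groups.** t(94) × √(2/48) = 0.405 SD, whatever r is.

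**Half-width if paired.** t(47) × √(2(1 − r)/48). The SD of the paired difference is √(2(1 − r)).

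| r (assumed) | SD of paired difference | Paired half-width | Unpaired ÷ paired | Actual coverage of the unpaired 95% interval |
|---|---|---|---|---|
| 0 | 1.41 SD | 0.411 SD | 0.99 | about 95% |
| 0.3 | 1.18 SD | 0.344 SD | 1.18 | 98.2% |
| 0.5 | 1.00 SD | 0.290 SD | 1.40 | 99.5% |
| 0.7 | 0.77 SD | 0.225 SD | 1.80 | 99.97% |

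Coverage is by normal approximation. For complete pairs the point estimate is the same either way, because the mean of the differences equals the difference of the means.

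**Planning illustration.** Assume a difference of 0.5 SD, two-sided 5% and 90% power. A parallel-group trial needs 2 × (1.96 + 1.282)² / 0.5² = 84.1, so 85 per arm, and the group SD is the right input. A within-patient trial needs (1 − r) times 84.1 patients: 85, 59, 43 and 26 at r = 0, 0.3, 0.5 and 0.7. Planning a within-patient trial from group SDs as if r were 0 would therefore ask for 85/59 = 1.4, 85/43 = 2.0 or 85/26 = 3.3 times as many patients as needed at the last three values.

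**The case against.** The strongest reply is that section 8.2 never prescribes an unpaired interval. It names no two-sample formula and no independence assumption, and a paired mean difference is also a difference in means. The within-patient design is plain in sections 3.1 and 5.4.1, and the interval formula and any baseline covariate are details that a protocol commonly leaves to a statistical analysis plan. That stands: a reader might infer that the reported intervals will be wrong, but the document supports this only if its two-group wording is followed literally. What remains is more than silence, because the parallel label contradicts the intra-patient design in the same sentence, and section 8.2 then carries two-group language into the estimation method.

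Three further points on the other side also stand.

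- **Direction.** With positive correlation an unpaired interval is too wide, not too narrow. The estimate is unaffected for complete pairs, and no test depends on it.
- **Planning SD.** A reader might infer that the pilot will yield the wrong SD for the main trial. Section 8.2 does not say whether that trial will be within-patient or parallel-group. For a parallel-group trial the group SD is the one needed, and the paired SD can still be computed from the scar-level data.
- **Baseline.** The allocation is randomised, so an unadjusted difference remains valid. Leaving out baseline costs precision only.

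For dichotomous endpoints section 8.2 plans counts and percentages without an interval, so no interval is at fault there.

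**Conclusion.** The concern holds as an avoidable ambiguity and a free improvement, not as a demonstrated error in the results. Section 8.2 describes a within-patient comparison as two groups, section 3.1 reinforces that with a contradictory label, and neither pairing nor baseline is named.

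If the text were followed as two independent samples, 95% intervals with 48 completers would be 18%, 40% and 80% too wide at correlations of 0.3, 0.5 and 0.7, and practically unchanged at 0. The size rests entirely on a correlation that the Protocol does not give and that this pilot is well placed to estimate. The consequence for planning applies only if the main trial is again within-patient.

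**What to change.** 1. **Effect and interval.** State in section 8.2 that, for outcomes measured on both scars, the treatment effect is the mean within-patient laser-minus-control difference at the final follow-up, with a paired 95% interval. Estimate it by regressing that difference on the baseline laser-minus-control difference; the intercept is the effect at equal baselines. A mixed model with a patient random effect and each scar's baseline is a reasonable alternative, but it is not the same model unless the patient's mean baseline is also included.
2. **Time point.** Sections 2.2.1 and 7.5.6 and Appendix A place the final assessment 6 months after the third laser treatment. Section 8.2 places it 12 months after the third treatment and ties the primary analysis to a 12-month assessment. Reconcile these before fixing the time point of the effect.
3. **Planning quantities.** Report the SD of the paired difference and the within-patient correlation beside the group SDs. Together they serve either design of main trial.
4. **Scope.** Keep patient-level outcomes out of this contrast: EQ-5D, blood markers, and BBSIP unless it is completed separately for each scar (section 7.3.4.3 describes overall impact). Also keep out the biopsy time points with tissue from the intervention area only (sections 7.5.3 and 7.5.5).
5. **Label.** Delete the words parallel assignment from section 3.1.

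The cost is wording. The scar assessments and the baseline and final biopsies are already scheduled on both scars, so no new data are needed.

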# STUDY OBJECTIVES

## Objectives

- - 1. **Primary Objectives**

To assess the kinetics of the response to fractionated CO_2_ laser therapy in hypertrophic scars, in particular to test the hypothesis that a positive effect on the scar (assessed through objective and subjective measures) is associated with reduced number of myofibroblasts and the increased presence of senescent skin cells.

- - 1. **Secondary Objectives**

To determine associations between the various cellular and molecular biomarkers and reduction in scarring post laser therapy.

To evaluate the extent to which the use of Brisbane Burn Scar Impact Profile (BBSIP) is a sound psychometric measure of improvements in scarring and the impact on participant’s quality of life as a result of laser treatment.

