**2.2.2 Secondary endpoints**

The secondary endpoints include: subjective (BBSIP, POSAS and mVSS) scores and objective assessment of the areas of interest on Months 3, 6 and 12 after first laser treatment. Objective assessment includes; 3D (Vectra H1) photography, scar thickness and density using Ultrasound (Derma scan cortex Denmark), pliability (Cutometer) and scar colour and pigmentation using DSM Colorimeter .

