# DATA MANAGEMENT & STATISTICS

## Determination of Sample Size

**8.1.1 Laser Treatment and Standard of Care**

Following recommendations for pilot studies, 30 patients or more are typically required to gain estimates of the parameters needed for sample size estimation. No formal sample size calculation has been performed as a result. We have allowed for a 20% drop-out and possible loss to follow-up. We therefore aim to recruit 60 participants in total. This will also allow the recruitment and retention rates to be estimated with 95% confidence interval maximum widths of 20% and 25% respectively.

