The primary analysis for the trial will occur once all participants have completed the 12 month assessment and corresponding outcome data has been entered onto the trial database, validated as being ready for analysis, and the database locked. This analysis will include data items up to and including the 12 month assessment.

For the secondary outcome data about the biomarkers of the scar response to laser therapy the various cellular and molecular variables will be examined for relationships to scarring using logistic regression. Further longitudinal analysis to identify potential drivers of a positive response will be done using linear mixed-effects modelling.

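### Logistic regression is the first-named model for biomarkers against scarring, although the objective is a degree of change and the scar instruments give graded or continuous values; in binary form it needs an undefined cut that discards information

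*Protocol*

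**What the plan says.** The secondary objective in section 2.1.2 is "To determine associations between the various cellular and molecular biomarkers and reduction in scarring post laser therapy". The scar outcomes in section 2.2.2 are "subjective (BBSIP, POSAS and mVSS) scores and objective assessment of the areas of interest", the objective part being 3D photography, ultrasound thickness and density, pliability and colour.

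Section 8.2 names the model for the biomarkers: "the various cellular and molecular variables will be examined for relationships to scarring using logistic regression". It gives no dependent variable, responder definition or threshold. The next sentence adds: "Further longitudinal analysis to identify potential drivers of a positive response will be done using linear mixed-effects modelling".

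Earlier in section 8.2 the type of data is to decide the method. The VSS total is the example of a continuous endpoint, and improvement by scar domain is the example of a dichotomous one, to be summarised as numbers and percentages. The analysis as a whole is to be descriptive and "mainly focus on confidence interval estimation, with no formal hypothesis testing performed".

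On size, section 8.1.1 says "We therefore aim to recruit 60 participants in total", "We have allowed for a 20% drop-out and possible loss to follow-up" and "No formal sample size calculation has been performed as a result".

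**The concern.** The model named first does not match the scale of the data or the question. How far a scar improved is a matter of degree, and the instruments record degree. A binary logistic model keeps only which side of a cut each scar falls on: a scar just past the cut counts the same as one far past it. The estimated association is then less precise, and it depends on where the cut lies.

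Precision is what this pilot is meant to deliver. Its results are confidence intervals, and its sample is small against a long list of candidate markers (sections 2.2.1 and 7.4.1.1). A threshold supplied later in an analysis plan would settle the definition but would not recover the discarded information. The point is therefore about the model the protocol has fixed, and goes beyond a missing detail.

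**Working it through.** **1. Scale of each scar measure, from the protocol**

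| Measure | Section | Scale |
|---|---|---|
| VSS | 7.3.4.1, 8.2 | items 0-4, 0-4, 0-3 and 0-3, so a total of 0 to 4+4+3+3 = 14; the total is treated as continuous in 8.2 |
| POSAS | 7.3.4.2 | two scales of six items, ten steps each |
| Ultrasound | 7.3.5.2 | thickness in mm; density in percent |
| Cutometer | 7.3.5.3 | mean of three measurement cycles |
| Colour | 7.3.5.1 | quantified melanin, erythema and reflectance |

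None is yes/no as collected. A binary outcome has to be derived from them.

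**2. The plan's own figures**

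The protocol gives no precision or power for the biomarker analysis, so there is no figure to reproduce there. Its nearest precision statement is a maximum 95% interval width of 25% for retention. With 60 participants this reproduces: 2 × 1.96 × √(0.25/60) = 25.3%. Evaluable patients after the stated drop-out: 60 × (1 − 0.20) = 48.

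**3. Information kept when the outcome is cut**

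Assumptions, none of them from the protocol: one biomarker value and one scar change per patient, bivariate normal, with a weak correlation r; the scar change is cut at the standardised value c, so that a proportion p are responders.

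- On the full scale, the information per patient about the association is proportional to r².
- After the cut, the covariance of the standardised biomarker with the yes/no outcome is r·φ(c), and the outcome variance is p(1−p). The information is proportional to r²·φ(c)²/[p(1−p)].
- The fraction kept is therefore E = φ(c)²/[p(1−p)]. The equivalent number of patients is 48·E, and the effective interval width is multiplied by 1/√E.

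| Responders p | c | φ(c) | E | 48·E | 1/√E |
|---|---|---|---|---|---|
| 50% | 0 | 0.399 | 0.159/0.25 = 0.64 | about 31 | 1.25 |
| 30% | 0.524 | 0.348 | 0.121/0.21 = 0.58 | about 28 | 1.32 |
| 20% | 0.842 | 0.280 | 0.078/0.16 = 0.49 | about 24 | 1.43 |

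A slope and a log odds ratio are on different scales, so the last column is width relative to the size of the association.

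**4. Cross-check by simulation**

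With 20,000 runs per setting and a two-sided 5% level used only as a yardstick, linear regression on the full scale was compared with logistic regression after a median split, at n = 48:

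| r | Full scale | Logistic, likelihood-ratio | Logistic, Wald |
|---|---|---|---|
| 0.2 | 28% | 21% | 17% |
| 0.3 | 55% | 40% | 35% |
| 0.4 | 82% | 65% | 60% |
| 0.5 | 97% | 85% | 81% |
| 0.6 | 100% | 97% | 95% |

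The direction agrees with step 3. The size depends heavily on the settings. Over r from 0.2 to 0.6, n of 48 or 60, and 50%, 30% or 20% responders, the loss runs from about 1 point (n = 60, r = 0.6, median split, likelihood-ratio) to 37 points (n = 48, r = 0.4, 20% responders, Wald).

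**The case against.** **The mixed model already covers it.** A linear mixed-effects model can keep the continuous outcome and the repeated visits, so a reader would be wrong to infer that the logistic model is the only biomarker analysis. That stands. But section 8.2 introduces the mixed model as a further, longitudinal analysis, after giving the relationship between biomarkers and scarring to logistic regression. It adds to the logistic step without replacing it.

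**A dichotomous improvement endpoint is planned.** It is, in section 8.2. But it has no threshold, is only to be counted, and is not named as the outcome of the logistic model. It too would have to be derived from graded scores.

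**Logistic regression need not be binary.** This is correct. A proportional-odds model needs no cut, and the protocol's words do not exclude it, so the documents do not show that every score must be cut. Nor do they say that ordinal regression is meant. The point applies to the ordinary binary reading.

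**The cut may be in an analysis plan.** It may. The missing definition alone would not be a finding, and nothing in the protocol says that a cut would be chosen after seeing the data. The loss of information remains wherever the cut is written down.

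**The design is richer than one value per patient.** True. The intervention scar is biopsied at four visits and the control scar at two (Appendix A), and the scars are assessed repeatedly. The calculation is a simplification that isolates the effect of cutting.

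**Conclusion.** The concern holds as a choice of a weaker method for the stated objective. If the logistic regression is binary, it keeps about 64%, 58% or 49% of the information at 50%, 30% or 20% responders. With 48 evaluable patients that equals about 31, 28 or 24 patients, or intervals effectively about 25%, 32% or 43% wider. These figures rest on bivariate normality, a weak association, one observation per patient and the full 20% drop-out.

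Two stronger conclusions are tempting and are not supported:

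- **A fixed loss of power for this trial.** The protocol states no power, correlation, significance level or cut, and plans no formal hypothesis testing. The simulated loss of about 1 to 37 points reflects the chosen settings. Loss of precision, stated conditionally, is the apt measure.
- **A limit of about two predictors under a ten-events rule.** That presumes a median split and one joint model. The protocol says only that the variables will be examined.

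The matter should be corrected, but it concerns an exploratory analysis in a pilot and does not undermine the trial.

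**What to change.** In section 8.2, replace the logistic regression with a linear regression of the continuous scar change on each biomarker, adjusted for the baseline scar value, and report the slope with its 95% CI. The change would run from baseline to the visit 6 months after the third laser treatment (section 7.5.6 and Appendix A). Use proportional-odds (ordinal logistic) regression for coarse ordinal items. Keep the linear mixed-effects model for the longitudinal data, and keep any binary analysis of improvement descriptive.

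The cost is one sentence of text, with no new data, patients or procedures. The small downside is that a slope is slightly harder to explain than an odds ratio of response.
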